## Abstract

**Background:**

Atopic eczema (AE) is a common atopic inflammatory skin disease affecting 2.1–4.9% of the population in different countries. Pruritus, one of the most burdensome symptoms, is often underestimated for the problems it can cause, creating a vicious loop of itching, scratching, and lichenification. Therefore, further research into practical and safe treatments that relieve itchy symptoms and enhance skin protection is key to overcoming AE. Acupuncture, with or without electrical stimulation, is one of the most commonly used therapeutic measures to treat AE. This trial aimed to objectively evaluate the efficacy and safety of the electroacupuncture (EA) antipruritic technique in AE pruritus and obtain high-level clinical evidence for the popularization and application of EA for AE.

**Methods and analysis:**

This multicenter, single-blinded, randomized controlled trial is planned to transpire from April 15, 2023, to June 30, 2025. We will recruit 132 participants with AE (44 per group). Participants will be assigned randomly to three equal-sized groups: EA, sham electroacupuncture, and sham acupuncture. Treatment will be administered three times a week during the 2-week intervention phase. The primary outcome measure is the Visual Analog Scale, with a numeric rating scale to evaluate pruritus. Secondary outcome measures include the Eczema Area and Severity Index and Dermatology Life Quality Index. Other outcome measures include physical examination, serum IgE, and safety evaluation. The number, nature, and severity of adverse events will be carefully recorded.

**Trial registration:**

ClinicalTrials.gov, 22Y11922200. Registered 3 September 2022, https://register.clinicaltrials.gov.

## Introduction

Atopic eczema (AE) is a common inflammatory condition characterized by itchy, scaly, erythematous, and oozing skin. The prevalence of AE in adults ranges from 2.1 to 4.9% in different countries (1). Confusion and inconsistency in their usage have resulted from the concurrent use of words including “eczema,” “atopic eczema,” “atopic dermatitis,” and “atopic eczema/dermatitis syndrome” (2). Therefore, “atopic eczema” has been proposed as a unifying term by the World Allergy Organization’s nomenclature review committee and is used throughout the text of this protocol (3).

Clinically, AE is usually classified into acute, sub-acute, and chronic types according to the lesion’s appearance. Erythema, papules, vesicles, and serous effusion are signs of acute lesions (4). Chronic AE is characterized by symmetry, serous exudate, pruritus, and recurrence; its symptoms include intractable itching, lichenification, and hyperpigmentation (5).

Itching is a burdensome symptom of AE and can lead to scratching, which can increase lesion inflammation and cause secondary skin infections. Reducing scratching behavior reduces lesion inflammation and promotes skin healing (6, 7). Itch-scratching behaviors lead to sleep disturbance, sleep-related impairment, and even physical and psychological disorders (8, 9). Skin lesions from long-term scratching progress to lichenification, creating a vicious cycle of “itching, scratching, and lichenification” that triggers and exacerbates AE (10). AE’s relapsing and remitting nature makes controlling intractable itching a challenge, considerably burdens a patient’s cost of living, and seriously affects their quality of life (5). Therefore, controlling itching is an important objective of AD treatment.

AE is a complex atopic skin disease caused by multiple factors, including genetic, external, environmental, and other factors affecting pathogenesis. The most commonly used clinical treatments for pruritus associated with AE include topical corticosteroids (TCS) and oral H1-antihistamines.

TCSs are an effective first-line treatment for AE. However, dependency and TCS withdrawal (addiction) are common; prolonged and extensive TCS use can result in adverse skin and systemic effects (11). Consequently, patients tend to have negative feelings toward TCS (12). Since TCS phobia decreases patient compliance, it is a major factor in treatment failure in patients suffering from AE (13). Therefore, TCS may be insufficient for controlling pruritus in AE.

The *American Academy of Dermatology* (AAD), *the European guidelines for chronic pruritus*, and a position paper from *the International Society of Atopic Dermatitis (ISAD)/Oriented Patient-Education Network in Dermatology (OPENED)* advise against the general use of H1-antihistamines for managing AE (14–17). However, they remain commonly used in the clinic because of their clinical efficacy in sedating, relieving itching, and improving sleep disturbances (15). The older first-generation H1-antihistamines are discouraged for long-term use, especially in children, because of drowsiness and adverse effects on learning and cognitive functions. Although second-generation H1-antihistamines have fewer side effects and better efficacy, some cause drowsiness, and some have cardiotoxic effects. Moreover, both generations of H1-antihistamines burden liver and kidney functions (18, 19). Therefore, further research into practical and safe treatments that relieve itchy symptoms and enhance skin protection is important for overcoming AE.

Acupuncture has recently gained importance in dermatology as a common complementary and alternative medicine therapy (20). With or without electrical stimulation, acupuncture can reduce lesions, ease itching, and improve patient quality of life (21–24).

Based on an animal study, acupuncture is more effective than other histamine-independent pruritogens (chloroquine) or histamine-dependent pruritogens (compound 48/80). The powerful inhibitory effects of acupuncture on serotonergic itch are likely caused, at least in part, by inhibiting 5-HT2 and 5-HT7 receptors (25, 26). Electroacupuncture (EA) has been shown to alleviate itch and flare in healthy human adults after intradermal histamine injection (27–29). Animal studies have shown that EA relieves pruritus; the underlying anti-inflammatory effects are closely linked to dynorphin release (30). Later research suggested that the vagal–adrenal anti-inflammatory axis is likely mediated by PROKR2ADV sensory fibers that innervate the deep limb fascia by low-intensity electropuncture stimulation. These studies provide a neuroanatomical basis for the selectivity and specificity of acupoints in driving specific autonomic pathways (31).

High-quality randomized controlled trials remain lacking despite various clinical studies on acupuncture therapy for AE in the treatment of pruritus. This study proposes a design for a multicenter, randomized, sham electroacupuncture–controlled protocol aiming for an objective and standardized evaluation of the acupuncture antipruritic technique’s effect on pruritus, clinical efficacy, and safety in AE to obtain definitive clinical evidence. The ultimate goal is to develop a clinical protocol suitable for standardizing the widely used acupuncture antipruritic techniques for AE.

## Methods and analysis

### Study setting

This multicenter, single-blinded, randomized controlled trial will be conducted in the Yueyang Hospital of Integrated Traditional Chinese and Western Medicine and the Shanghai Skin Disease Hospital in China. The trial has been registered at ClinicalTrials.gov (ID: 22Y11922200). At the time of writing this report (version 2.0, January 4, 2023), the trial has not yet begun enrollment. Participant recruitment will take place from April 15, 2023, to June 30, 2025. This protocol has been developed according to Standard Protocol Items: Recommendations for Interventional Trials (SPIRIT) 2013. The checklist is presented in detail in Supplementary Table 1.

### Sample size

According to a previous study (32), the mean itch intensity was taken as 35.7% for the EA group, 40.4% for the sham electroacupuncture (SEA) group, and 45.9% for the sham acupuncture (SAC) group, with *α* = 0.05, test efficacy 1-β = 0.8, two-sided test, using the estimation of sample size formula for comparing more than two treatment groups [referring to 
$n=2{\left(\sigma \frac{Z_{1-\alpha /\left(2\tau \right)}+Z_{1-\beta }}{\mu_{A}-\mu_{B}}\right)}^{2}$
, 
$1-\beta =\Phi \left(Z-Z_{1-\alpha /\left(2\tau \right)}\right)+\Phi \left(-Z-Z_{1-\alpha /\left(2\tau \right)}\right)$
, 
$Z=\frac{\mu_{A}-\mu_{B}}{\sigma \sqrt{\frac{2}{n}}}$
, where Φ is the standard normal cumulative distribution function, 
$\mu_{A}\;\mathrm{and}\;\mu_{B}$
 representing the mean of any two groups, and n is the sample size of a pair of τ comparisons (taking the maximum value)]. Consequently, the sample content was calculated to be 35 cases per group and 105 cases for the three groups. Assuming a 20% dropout rate of patients at follow-up, we calculated the sample size to be 44 cases for each group and 132 participants for the three groups (EA, SEA, and SAC). Participants will be recruited from two research centers, each targeting 66 participants.

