### Eligibility criteria

Inclusion criteria:

To be eligible for recruitment, the patient must:Be diagnosed with AE for a duration longer than 2 months.Be aged 18–65 years (male or female).Have body surface area (BSA) scores <10%.Provide consent to participate in clinical trial observation and cooperation with scheduled follow-ups.Sign and date the informed consent form.

Exclusion criteria:

Patients who meet any of the following criteria will be excluded:Have been systematically treated with drugs, such as hormones or immunosuppressants, within 2 weeks.Do not tolerate acupuncture.Signs of serious secondary infections, including localized skin infections and infections of other organs.Pregnancy, lactation, or planning to become pregnant during the trial.Diabetes or a combination of severe heart, liver, or kidney diseases.Received other investigational drugs or participated in other clinical trials within 3 months.BSA scores ≥10%.Unable to cooperate with the study for any reason, such as impaired language comprehension or inability to visit the study center.Generalized eczema with lesions spreading over the body is unsuitable for acupuncture.Acute flare-ups.

Drop-out exclusion criteria:

Patients who meet any of the following criteria will be a dropout case; if the time is past the mid-point of participation in the overall study, the data should be included in the efficacy statistics:Experienced unexpected events during treatment and are unfit to continue with the trial.Develop other illnesses during the course of the trial that affect judgments of efficacy and safety.Lack of compliance or voluntarily accepting other treatments during the course.Information is incomplete and affects judgments of efficacy and safety.Changed their contact details, resulting in loss of contact.

Exit/termination criteria:Patients who have experienced severe adverse reactions during treatment and whose treating physician assessed that the trial is no longer appropriate.Patients’ unsolicited requests to withdraw from the trial should be recorded, and the reasons noted.

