### Statistical analysis

Professional statisticians developed a statistical analysis plan upon consultation with the primary investigators. The data will be stored in the Data Management Center of Jiangsu Famous Medical Technology Co. Ltd. and processed by in-house statisticians blinded to group allocation.

All statistical analyses are performed using R [version 4.1.3; R Core Team (2022). R: A language and environment for statistical computing. R Foundation for Statistical Computing, Vienna, Austria^2^]. Statistical significance is set at value of *p* < 0.05. The intention-to-treat analysis population, consisting of all participants who pass the randomization stage, will be the primary population for demographic and other baseline characteristics, compliance, efficacy analysis, and safety analysis.

The analytical methods will be combined with descriptive and comparative analyses. Qualitative data will be described by frequency tables, percentages, or composition ratios; comparative analyses will be conducted using the chi-squared test, Fisher’s exact test, Wilcoxon rank-sum test, Cochran–Mantel–Haenszel test, and weighted least-squares covariance. Quantitative data will be described as the mean, standard deviation, median, quartile, minimum, and maximum. The *t*-test will be used for comparative analysis of data with normal distributions and with Satterthwaite correction if the variance is uneven. Quantitative data exhibiting a non-normal distribution on the Wilcoxon rank-sum test will be analyzed using the Wilcoxon signed-rank sum test and covariance generalized linear models. A sensitivity analysis for the primary outcome with the most conservative data (the worst or best outcome of that indicator in the group) will assess the robustness of the missing data at random assumption. A multiple imputation will be used to impute missing values.

The hypothesis test is two-sided; the test statistics and their corresponding *p*-values will be reported.

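### Reachable participants who stop or switch treatment become dropout cases, with their data used only past the mid-point, which conflicts with the all-randomized primary analysis

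*Protocol article*

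**What the plan says.** In the Protocol article, Eligibility criteria, the drop-out list opens with "Patients who meet any of the following criteria will be a dropout case". It adds that data are used in the efficacy statistics if the participant is past the mid-point of participation. The five reasons are an unexpected event that leaves the person unfit to continue, another illness, "Lack of compliance or voluntarily accepting other treatments during the course", incomplete information, and loss of contact. Severe adverse reactions and participants' own requests to withdraw stand in a separate exit list.

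The Sample size section reaches its base figure first: "the sample content was calculated to be 35 cases per group and 105 cases for the three groups". It then allows for loss: "Assuming a 20% dropout rate of patients at follow-up, we calculated the sample size to be 44 cases for each group".

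The Outcome measures section makes VAS improvement after 2 weeks primary, with VAS taken at screening, week 1 and week 2. The Statistical analysis section names the intention-to-treat set (everyone randomized) as primary for efficacy and states "A multiple imputation will be used to impute missing values". It also plans a sensitivity analysis with worst or best outcomes to test the missing-at-random assumption.

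**The concern.** An intention-to-treat comparison needs the week-2 VAS of everyone randomized, whatever happened to their treatment. The drop-out list treats stopping or changing treatment as if it were leaving the study. A participant who misses sessions, falls ill or takes another remedy has not thereby become unreachable. The outcome is a self-rated score due after 2 weeks of treatment, so it is easy to obtain.

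What is at stake is bias. People who are non-compliant or turn to another treatment plausibly do so because of their itch, and the reasons can differ by arm, for example no relief under sham or discomfort under current. If their scores are left out, or filled in as though they resembled the scores of completers, the contrast between arms can shift in a direction that nobody can check afterwards.

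**Working it through.** **1. The plan's own figure.** Inputs from Sample size: 35 evaluable per arm, 20% dropout; from Randomization and allocation: 1:1:1.
- 35/(1 − 0.20) = 43.75, rounded up to 44; 3 × 44 = 132. This matches.
- Planned loss: 132 × 0.20 = 26.4, about 26 participants. Evaluable per arm: 44 × 0.80 = 35.2.
- Dividing by 0.80 gives each dropout zero weight in the primary comparison.

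**2. Who on the list can still be measured?**
- Unfit to continue after an unexpected event: usually yes.
- Another illness: usually yes.
- Non-compliance or other treatment: yes.
- Incomplete information: unclear, because it describes data already missing.
- Loss of contact: no.

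Three of the five reasons clearly describe reachable people. The article does not split the 20% by reason, so their share of the 26 is unknown.

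**3. What the mid-point rule does.** The study lasts 3 weeks, 1 of screening and 2 of treatment. The mid-point is therefore 1.5 weeks from the start, or 0.5 weeks into treatment; counting treatment only, it is week 1. Either way it precedes the week-2 VAS. So a dropout before the mid-point is, by implication, outside the efficacy statistics. A dropout after it is included, but has a week-2 VAS only if someone goes on to collect it.

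**4. Side by side.** Eligibility criteria admits dropout data conditionally on timing. Statistical analysis admits everyone randomized and imputes gaps. A randomized participant who stops before the mid-point is out under the first and in under the second. The Blinding section points the same way as the first: it pairs being counted as a dropout with censoring the data.

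**5. Would fuller collection raise power?** Inputs: α = "0.05, test efficacy 1-β = 0.8, two-sided test, using the estimation of sample size formula for comparing more than two treatment groups"; the smallest planned difference, EA against SEA, is 40.4 − 35.7 = 4.7, and it governs because n "is the sample size of a pair of τ comparisons (taking the maximum value"). Neither σ nor τ has a stated value, so I solve for σ at τ = 1 and τ = 3:
- σ = 4.7/[(z(1 − 0.05/(2τ)) + 0.842) × √(2/35)] = 7.02 (τ = 1) or 6.08 (τ = 3).
- All 44 measured and all carrying the full 4.7: power 88.1% (τ = 1) to 89.1% (τ = 3).
- The 9 recovered per arm (44 − 35) carry no effect: the contrast is 4.7 × 35/44 = 3.74. At τ = 1, Z = 3.74/(7.02 × √(2/44)) = 2.50, and Φ(2.50 − 1.96) is about 70%. At τ = 3, Z = 2.88, and Φ(2.88 − 2.39) is about 69%.
- The 9 carry half the effect: the contrast is 4.7 × 39.5/44 = 4.22, and power is about 80% for either τ.

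Power can go up, stay level or fall, depending on how stoppers respond.

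**The case against.** The strongest reply is that this is a condensed article. The full protocol and the schedule figure are not shown, and follow-up after stopping sessions is often set out there. No visible sentence says that VAS collection ends for dropouts, and data after the mid-point are expressly used. That much stands: silence on continued collection would not be a finding by itself. What the article does state is the rule that makes these reachable people dropout cases and admits their data by timing. That rule disagrees with the analysis population whatever the full protocol adds. The mid-point rule might be meant for a secondary set, but the article names no such set.

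The worst/best-outcome sensitivity analysis is a genuine safeguard. It can probe the missing-at-random assumption, but it cannot stand in for an observed score.

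A reader might go further in five ways, none of which the documents support:
- That the Sample size section writes off a fifth of the participants. The 20% is a planning allowance, correctly applied.
- That observable scores will be replaced by imputation. For early dropouts the text implies exclusion at least as much.
- That four of the five reasons describe reachable people. Incomplete information does not clearly do so.
- That better retention brings power of 88% to 89%. This assumes that stoppers keep the full effect, which contradicts the reason for worrying about them.
- That the bias can be stated in points. It needs dropout by arm and the distance of true from imputed scores, and the article gives neither.

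**Conclusion.** The point holds as an inconsistency between the drop-out rule and the intention-to-treat analysis, and it should be corrected. Its reach is bounded by the planned allowance of about 26 of 132 participants. The part that clearly reachable people make up is unknown, as is the size of any bias.

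The conclusion rests on two judgements. One is that people who are unfit to continue, ill, non-compliant or on other treatment can usually still give a self-rated score. The other is that their missingness is plausibly related to itch and to arm. The sample size arithmetic is right and 44 per arm need not change. The benefit of correcting this is less bias and agreement between sections, not power.

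**What to change.** In Eligibility criteria, separate stopping treatment from leaving the study:
- Keep everyone who has not withdrawn consent or been lost to contact under outcome collection: week-1 and week-2 VAS and DLQI on the scheduled days, by telephone or online form if they do not attend.
- Reserve the word dropout for withdrawn consent or lost contact.
- Include the collected values in the intention-to-treat analysis regardless of the mid-point, and remove or reconcile the mid-point condition.
- Impute only values that remain missing, and keep the worst/best-outcome sensitivity analysis for those.
- Keep 44 per arm.

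This leaves untouched when or why treatment stops. The cost is protocol wording and a few remote contacts within the existing 2 weeks. The small downside is a contrast that includes values recorded after other treatment, which the all-randomized population already implies.

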### Eligibility criteria

Inclusion criteria:

To be eligible for recruitment, the patient must:Be diagnosed with AE for a duration longer than 2 months.Be aged 18–65 years (male or female).Have body surface area (BSA) scores <10%.Provide consent to participate in clinical trial observation and cooperation with scheduled follow-ups.Sign and date the informed consent form.

Exclusion criteria:

Patients who meet any of the following criteria will be excluded:Have been systematically treated with drugs, such as hormones or immunosuppressants, within 2 weeks.Do not tolerate acupuncture.Signs of serious secondary infections, including localized skin infections and infections of other organs.Pregnancy, lactation, or planning to become pregnant during the trial.Diabetes or a combination of severe heart, liver, or kidney diseases.Received other investigational drugs or participated in other clinical trials within 3 months.BSA scores ≥10%.Unable to cooperate with the study for any reason, such as impaired language comprehension or inability to visit the study center.Generalized eczema with lesions spreading over the body is unsuitable for acupuncture.Acute flare-ups.

Drop-out exclusion criteria:

Patients who meet any of the following criteria will be a dropout case; if the time is past the mid-point of participation in the overall study, the data should be included in the efficacy statistics:Experienced unexpected events during treatment and are unfit to continue with the trial.Develop other illnesses during the course of the trial that affect judgments of efficacy and safety.Lack of compliance or voluntarily accepting other treatments during the course.Information is incomplete and affects judgments of efficacy and safety.Changed their contact details, resulting in loss of contact.

Exit/termination criteria:Patients who have experienced severe adverse reactions during treatment and whose treating physician assessed that the trial is no longer appropriate.Patients’ unsolicited requests to withdraw from the trial should be recorded, and the reasons noted.

### Randomization and allocation

Once eligibility is confirmed and consent is obtained, participants will be block-randomized using a non-stratified, permuted block of varying lengths (*n* = 2 blocks; patient distribution = 1:1:1) for each group. Independent statisticians will provide computer-generated random sequences. Distribution will be conducted using a central web-based interactive randomization service system; the patients will be assigned randomly to three groups. Participant identification numbers will be provided to make identification easier throughout the trial. The researchers who perform random grouping will need to log onto the website to view the grouping situation of each eligible participant. The authors have no access to information that could identify individual participants during or after data collection.

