We propose a prospective, multicenter, randomized controlled study of AE. The multicenter model considers the effect of environmental factors and individual participant characteristics on trial results, providing more reliable clinical evidence. We designed three arms to compare the effectiveness of EA and acupuncture and to establish the genuineness and credibility of the acupoints while eliminating any potential placebo effect. The objective VAS score was adopted as the primary outcome measure, and the EASI and DLQI scores as the secondary outcome measures, which should improve the reliability of the results. In addition, physical examination, personal life history, safety evaluation, patient satisfaction, and other outcome measures have been added. Keeping participants closer to the clinic helps track the disease progression in a clinical setting.

The study design has limitations. First, the sample size is only 132 participants. Second, the study duration is limited to 3 weeks without a follow-up period. Observing the long-term effects of the EA anti-itch technique on the progression of AE with a limited sample size and follow-up period will be challenging. However, we will use unique experimental designs and outcome measures to improve the accuracy and sensitivity of this study to mitigate these limitations.

In summary, this multicenter, randomized, sham electroacupuncture–controlled study will assess the effect on pruritus, clinical efficacy, and safety of the acupuncture antipruritic technique in AE. We will also establish a multicenter clinical registration platform and evaluate clinical evidence by assessing the treatment’s therapeutic benefits (clinical effectiveness with no adverse side effects). The findings will aid decision-making for managing and treating AE and offer crucial data that could be integrated into future clinical recommendations.

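### Randomisation is explicitly not stratified although two centres recruit 66 patients each, so arms can be unbalanced within centre; separately, the block specification is ambiguous

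*Protocol article*

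**What the plan says.** All references are to the protocol article.

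- **Randomization and allocation:** "participants will be block-randomized using a non-stratified, permuted block of varying lengths". The parenthesis that follows refers to "2 blocks; patient distribution = 1:1:1) for each group". No block length is given.
- **Same section, on delivery:** "Distribution will be conducted using a central web-based interactive randomization service system". No list per centre is mentioned, and the word non-stratified rules one out.
- **Sample size:** "Participants will be recruited from two research centers, each targeting 66 participants", with "44 cases for each group and 132 participants for the three groups (EA, SEA, and SAC").
- **Blinding:** the treating physicians cannot be blinded, and each hospital designates several operators of its own.
- **Discussion:** "The multicenter model considers the effect of environmental factors and individual participant characteristics on trial results".
- **Study setting:** enrolment had not begun when this version was written.

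**The concern.** With two centres and unblinded operators specific to each hospital, centre is an obvious factor on which to balance. Operator manner, local practice and setting can all act on a patient-reported itch score. If one arm happens to be treated more often at one hospital, part of any hospital or operator difference appears in an unadjusted comparison of arms. Randomisation makes this a matter of chance, with no systematic direction, but a single trial gets only one draw. Lack of stratification is a choice the article states, so it cannot be put down to condensation.

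The block parenthesis is a second, independent matter. A statistician asked to generate the list from that sentence would have to guess what the number 2 refers to. The reference to each group does not fit either, because a block spans all three groups.

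**Working it through.** **Inputs.** From Sample size: 35 evaluable per group, 20% dropout, three arms, two centres. From Randomization and allocation: 1:1:1, non-stratified, varying block lengths. Assumed, because the article gives no figure: block lengths of 3 and 6 (alternatively 6 and 9), and patients of the two centres arriving in random order.

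**The plan's own figures.** 35 / (1 − 0.20) = 43.75, rounded up to 44 per group. 3 × 44 = 132, and 132 / 2 = 66 per centre. All agree with the article. Perfect balance within a centre is 66 / 3 = 22 per arm. The step that leads to 35 cannot be reproduced because no SD is stated, but nothing here depends on it.

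**Spread of one arm at one centre, single list.** With 44 EA patients among 132 and 66 places at centre 1, the count is approximately hypergeometric:

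- Variance = 66 × (1/3) × (2/3) × (132 − 66)/(132 − 1) = 14.667 × 0.5038 = 7.39
- SD = √7.39 = 2.72

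**Gap between largest and smallest arm at a centre** (5,000 simulated trials per row):

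| Scheme | Median | 95th percentile | Maximum | P(gap ≥ 5) | P(gap ≥ 10) |
|---|---|---|---|---|---|
| One list, blocks 3 and 6 | 5 | 11 | 19 | 62% | 12% |
| List per centre, blocks 3 and 6 | 0 | 2 | 2 | 0 | 0 |
| One list, blocks 6 and 9 | 5 | 11 | 20 | 61% | 10% |
| List per centre, blocks 6 and 9 | 0 | 2 | 3 | 0 | 0 |

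The choice of valid block lengths hardly matters. The imbalance comes from not stratifying.

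**What it does to an unadjusted comparison.** The shift equals the between-arm difference in the share treated at centre 1, multiplied by the difference between centres.

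- Covariance of two arm counts = −66 × (1/9) × (66/131) = −3.69
- Variance of the difference in counts = 2 × 7.39 + 2 × 3.69 = 22.2, so SD = 4.71
- SD of the difference in shares = 4.71 / 44 = 0.107; 95th percentile of its absolute value about 0.20 (simulation)
- If the centres differed by 5 to 15 points on a 0–100 itch scale (an assumption; the article gives nothing), the 95th-percentile shift is 0.20 × 5 = 1 point to 0.20 × 15 = 3 points. The planning difference between EA and SEA is 40.4 − 35.7 = 4.7 points.

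**Efficiency.** For a 27:17 split of two arms within a centre, relative to 22:22: (1/22 + 1/22) / (1/27 + 1/17) = 0.948. Over 20,000 simulated trials with blocks of 3 and 6, a centre-adjusted EA–SEA comparison keeps 98.8% of full efficiency on average, and at least 95.8% in 95% of trials.

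**Readings of the block parenthesis.** A 1:1:1 block must have a length divisible by 3.

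- Block length 2: impossible for three arms, and not a varying length.
- Two block lengths, for example 3 and 6: valid.
- Two blocks in total, 66 each with 22 per arm: balanced at the end of each block, but hard to square with varying lengths.

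**The case against.** Non-stratified permuted blocks are a legitimate scheme. Allocation is unbiased and overall arm sizes stay within 2 or 3 of each other in the simulations. Head counts by centre do not by themselves show harm: if the centres differed by half an outcome SD (assumed), the chance shift would have SD 0.5 × 0.107 ≈ 0.05 outcome SD, against a standard error of √(2/44) ≈ 0.21 outcome SD for the comparison. All of this stands, and it limits the weight of the point.

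Several stronger conclusions that a reader might draw are not supported:

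- *That the stated blocks cannot be balanced.* This is true only if the 2 is a block length. Two block lengths is a natural reading, and it works.
- *That the block wording causes the imbalance within centres.* It does not; the imbalance arises equally with valid blocks.
- *That centre is left out of the analysis.* Statistical analysis refers to a separate plan that is not shown. It also lists the Cochran–Mantel–Haenszel test and covariance methods without naming strata or covariates. Adjustment for centre may already be planned.
- *That the two hospitals treat different populations.* The article describes neither population and applies the same eligibility criteria to both.
- *That the Discussion is contradicted.* Its remark on the multicentre model is general and promises no balance within centres.

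What remains is that the scheme gives up balance on a known factor when keeping it would cost almost nothing.

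**Conclusion.** The point holds as a recommended improvement. A two-centre trial with operators specific to each hospital uses an explicitly non-stratified list, so balance within a centre is left to chance: SD about 2.7 around 22 for each arm, and a gap between largest and smallest arm with median 5 and 95th percentile 11, against at most 2 with a list per centre and the same blocks. These figures assume block lengths of 3 and 6, 66 patients per centre and random order of arrival. If one centre recruited in long runs, more blocks would fall wholly inside a centre and the gaps would be smaller.

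The consequence is possible chance confounding of arm with centre or operator. Its size depends on a centre difference that the documents do not give, and it largely disappears if the analysis adjusts for centre. There is no systematic bias and little loss of efficiency. The block parenthesis is ambiguous and needs rewording, but it does not show that the scheme is unworkable.

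**What to change.** In Randomization and allocation:

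1. Stratify the central randomisation by centre, with one list per hospital.
2. State that block lengths vary at random, are multiples of three, and are withheld from the sites. The lengths themselves need not be published.
3. Delete the count of two blocks and the reference to each group.

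In the primary analysis model, include centre as the stratification factor, or confirm that the analysis plan already does so.

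The cost is one extra list in the existing web system and one covariate. With two lists the overall arm totals can differ slightly more, because each list may end on an incomplete block: the largest overall gap in the simulations was 4 instead of 2 with blocks of 3 and 6, and 6 instead of 3 with blocks of 6 and 9. That is minor with 44 per arm. The change to the lists belongs before the first patient is randomised. If allocation has already started on the single list, adjustment for centre in the model is still available.
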